### Participant flow, assessments and timeline

Independent Research Assistants (RAs) will assess participants at baseline within 2 weeks post-hospital discharge (T1) and again at 6 months (T2) and 12 months (T3) after baseline through a structured in-home interview. The study team will aim to complete all assessments at the participant’s place of residence, but completion by telephone is an option if participants prefer. Each assessment will take approximately 1–1 ½ half hours to complete. RAs with previous experience working in community-based settings will be trained in consent and data collection and management procedures. The Research Coordinator will meet with the RAs on a regular basis to address any questions and concerns and ensure consistency of approach across the three sites. The Research Coordinator will check the data at regular intervals during the data collection period in order to keep the number of errors and missing data as low as possible and gather maximum data for analysis. The flow of participants through the study phases will be presented using a flow diagram which conforms to the Consolidated Standards of Reporting Trials (CONSORT) guidelines for pragmatic trial reporting [39] (Fig. 2).

**Fig. 2 Fig2:**
[figure not shown]
Flow Diagram of Progress through Study Phases

### Sample size

The target sample size of 216 (72 from each of the three sites) was derived from the Mental Component Summary (MCS) score of the VR-12 [51], which assumes a power of 80%, alpha of 0.05, mean MCS score difference of 6.5, standard deviation of 15.0 and 20% attrition, reported in the feasibility study [18].

### Recruitment

Trained recruiters will be identified at participating sites and will receive training about the CAST intervention and eligibility criteria. These individuals will approach potentially eligible patients prior to hospital discharge to determine their interest in learning more about the study. A standardized screening script will be used to introduce the patients to the study. At one site, permission from a member’s circle of care is required before the recruiter approaches the patient.

If the patient agrees to be screened for study eligibility, an eligibility questionnaire will be completed, at which point the recruiter will confirm whether the patient is eligible. Eligible patients will then be asked if they were willing to be contacted about the study following discharge from hospital. Eligible patients who consent to be contacted by the Research Assistant upon discharge from hospital will receive a study information sheet. Participants will be enrolled in the trial after hospital discharge, once written informed consent is provided. Recruitment will occur over a 13-month period across the three study sites.

### Randomization and blinding

Within each study region, participants will be assigned to either the intervention or the usual care group following the collection of baseline data, using stratified permuted block randomization administered by a centralized web-based service (RedCap) to allocate clients at each site to the two groups in accordance with the sequence and using a 1:1 ratio. All study participants will be blinded to their group allocation (usual care or CAST intervention). Research assistants completing further assessments with participants following recruitment will remain blind to group assignments for the duration of data collection. Upon completion of the study at 12-months, participants will receive a mailed debriefing letter describing the two groups and their group allocation.

### Interventions

#### CAST intervention group

The CAST intervention was designed to complement usual care and consists of usual care plus a tailored patient- and caregiver-centred intervention delivered by a Care Transition Coordinator (CTC) who is a Registered Nurse (RN). The CTC will conduct a minimum of two in-home visits along with a minimum of four telephone calls scheduled to accommodate participant needs and preferences over a six-month period.

Throughout the 6 month duration of the intervention, the CTC will: 1) identify the health care professionals involved in the participant’s circle of care and initiate a plan for regular communication and follow-up with these individuals and organizations; 2) identify and manage the patient’s risk factors for depressive symptoms and other chronic conditions in accordance with evidence-based guidelines [52, 53]; 3) provide system navigation support, coordination, and follow up for participants and caregivers; 4) conduct medication review and management in collaboration with participants, primary care providers and pharmacists using evidence-based best practice guidelines [52, 53]; 5) conduct problem-solving therapy with participants and caregivers using Nezu et al.’s [54] manual; 6) implement social and behavioural activation, which involves assisting and encouraging participants to participate in regular physical activity programs tailored to social and behavioural needs; 7) provide patient and caregiver education; and 8) alert the participant’s primary care provider to the presence of depressive symptoms, dementia, delirium, suicidal ideation, or medication issues. These activities will be completed through direct interactions with participants during home visits and phone calls and indirect activities, (e.g., referring participants to health and social services, communicating with healthcare providers in the participant’s circle of care) completed between scheduled appointments.

This pragmatic trial is a tailored intervention with fixed and flexible elements that are adaptable to patient needs and preferences and the local context. Consistent with a pragmatic trial, participants allocated to the CAST intervention, can accept or decline as much of the intervention as they want. Examples of allowable adaptations include removing and/or integrating elements that overlap with routine or usual care. The CTCs will attend an 8-h training session supported by role-appropriate and standardized manuals. Training sessions will be led by the Principal Investigators and the Research Coordinator and include education and role-playing to enhance skills in problem-solving therapy within the context of MCCs.

#### Usual care group

Participants allocated to the control group at discharge from hospital to home will receive usual care. Usual care, which varies from site to site, may include recommendations for the patient to see their primary care provider and/or other medical specialists or access home care and/or other health and social services provided in the community after hospital discharge.

#### Effectiveness measures and data sources

The effectiveness of the CAST intervention on older adults and their caregivers will be evaluated using a range of patient and caregiver-relevant measures. A summary of these measures, including their description, related variables/outcomes, and time point(s) collected, and methods of analysis, are summarized in Table 1.

**Table 1 Tab1:** CAST Study Outcome Measures Summary

Outcome	Measure	Group*	Timepoint	Method of Analysis
Mental functioning	Mental Component Score of VR-12 (MCS) [51, 55]	PT, CG	T_1_, T_2_, and T_3_	-Descriptive analyses -T1-T2 (Treatment Effect): ANCOVA, complete case and multiple imputation analyses, subgroup analyses, quantile regression -T2-T3 (Sustainability): ANCOVA, complete case and multiple imputation analyses, subgroup analyses
Physical functioning	Physical Component Score (PCS) of VR-12 [51, 55]	PT, CG	T_1_, T_2_, and T_3_	-Descriptive analyses -T1-T2 (Treatment Effect): ANCOVA, complete case and multiple imputation analyses, subgroup analyses, quantile regression -T2-T3 (Sustainability): ANCOVA, complete case and multiple imputation analyses, subgroup analyses
Depressive symptoms	CESD-10 [56]	PT, CG	T_1_, T_2_, and T_3_	-Descriptive analyses -T1-T2 (Treatment Effect): ANCOVA, complete case and multiple imputation analyses, quantile regression -T2-T3 (Sustainability): ANCOVA, complete case and multiple imputation analyses
Anxiety symptoms	Generalized Anxiety Disorder scale (GAD-7) [57]	PT, CG	T_1_, T_2_, and T_3_	-Descriptive analyses -T1-T2 (Treatment Effect): ANCOVA, complete case and multiple imputation analyses, quantile regression -T2-T3 (Sustainability): ANCOVA, complete case and multiple imputation analyses
Perceived social support	Personal Resource Questionnaire (PRQ-2000) [58]	PT	T_1_, T_2_, and T_3_	-Descriptive analyses -T1-T2 (Treatment Effect): ANCOVA, complete case and multiple imputation analyses, quantile regression -T2-T3 (Sustainability): ANCOVA, complete case and multiple imputation analyses
Communication between patients and providers	Patient-Provider Communication questionnaire [59]	PT, CG	T_1_ and T_2_	-Descriptive analyses -T1: z test of proportions for group comparison, complete case analysis -T2: z test of proportions for group comparison, complete case analysis
Client-centredness of care	Adapted Client-Centred Care Questionnaire (CCCQ) [60]	PT, CG	T_1_, T_2_, and T_3_	-Descriptive analyses -T1: z test of proportions for group comparison, complete case analysis -T2: z test of proportions for group comparison, complete case analysis
Care experience	Integrated Care Patient-Reported Experience Measures (IC-PREMs) [61]	PT, CG	T_1_, and T_2_	-Descriptive analyses -T1: z test of proportions for group comparison, complete case analysis -T2: z test of proportions for group comparison, complete case analysis
Unmet care needs	Unmet Care Needs questionnaire	PT, CG	T_1_, T_2_, and T_3_	-Descriptive analyses - T1: z test of proportions for group comparison, complete case analysis -T2: z test of proportions for group comparison, complete case analysis
Caregiver strain	Modified Caregiver Strain Index (CSI) [62]	CG	T_1_, T_2_, and T_3_	-Descriptive analyses -T1-T2 (Treatment Effect): ANCOVA, complete case analysis -T2-T3 (Sustainability): ANCOVA, complete case analysis
Utilization of health and social services and associated costs	Institute for Clinical Evaluative Sciences (IC/ES), Health and Social Services Utilization Inventory (HSSUI) [63, 64]	PT, CG	T_1_, T_2_, and T_3_	-Descriptive analyses -T1-T2 (Treatment Effect): Mann-Whitney U test, complete case analysis, Hazard Ratio (95% CI) & Risk Difference (95% CI) for 30, 90 &180-day ED visits and hospital admissions -T2-T3 (Sustainability): Mann-Whitney U test, complete case analysis

*PT = patient; CG = caregiver, *T1 = baseline; T2 = 6-month; T3 = 12 months

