##### Cost of use of health and social services

The study will link participants to Institute for Clinical Evaluative Sciences (IC/ES) administrative databases to identify the use of emergency room visits, hospital admissions, use of family physicians, physician specialists, and home care services, and transfers to long-term care. In addition, the Health and Social Services Utilization Inventory (HSSUI) [63] will be used to measure the utilization of health and social services as reported by study participants and caregivers over the duration of the study. The HSSUI consists of questions about the respondent’s use of six categories of direct healthcare services: a) primary care; b) emergency department and specialists; c) hospital days; d) seven types of other health and social professionals; e) prescribed medications; and f) lab services. The data from the HSSUI will be used in combination with the IC/ES administrative data as a back-up in case we are unable to obtain IC/ES data at all three timepoints.

The six-month cost data will be derived from the product of “quantity” data reported on the HSSUI and 2015–2016 “price” data obtained by our team for the HSSUI [64]. The costs of use of health and social services will include the costs associated with delivery of the nurse-led intervention. This will form the basis of the cost-analysis, from a societal perspective that will compare changes in the costs of use of health and social services between participants in the intervention and control groups from baseline to 6- months, and from 6-months to 12-months post intervention. A complete copy of the HSSUI questionnaire is included as supplementary data (see Additional files 1 and 2). Table 1 provides an overview of the effectiveness evaluation, including the outcome, measures, group, and tiepoint for data collection.

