Subgroup analyses will be conducted for the VR-12 outcomes to determine if the intervention is effective for subgroups of patients from baseline to T2. The following baseline variables have been selected a priori for testing subgroup effects: age, sex, number of chronic conditions, depressive symptoms (CESD-10), site, and dose of the intervention (number of home visits and telephone contacts). Multiple imputation will be used to address missing data. All data analyses will assume a level of significance of 0.05 and be performed using SAS Version 9.4.

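### Service use and costs are planned as complete case only, with costs built on interview-reported quantities, although planned record linkage could cover much of the use of participants who miss an interview and the text promises multiple imputation without exception

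*Protocol article*

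**What the plan says.** Table 1 (under Effectiveness measures and data sources) has one row for service use and costs, covering patients and caregivers at T1, T2 and T3. For baseline to 6 months the method is "T1-T2 (Treatment Effect): Mann-Whitney U test, complete case analysis, Hazard Ratio (95% CI) & Risk Difference (95% CI", the last two items being for emergency visits and admissions at 30, 90 and 180 days. For 6 to 12 months it is "T2-T3 (Sustainability): Mann-Whitney U test, complete case analysis". The rows for MCS, PCS, CESD-10, GAD-7 and PRQ-2000 list complete case and multiple imputation together; this row lists complete case alone.

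The section Cost of use of health and social services states: "The study will link participants to Institute for Clinical Evaluative Sciences (IC/ES) administrative databases". The purpose is to identify emergency visits, admissions, family physician and specialist use, home care and long-term care transfers. Of the self-report inventory it says: "The data from the HSSUI will be used in combination with the IC/ES administrative data as a back-up", in case IC/ES data cannot be had at all three time points. Its next paragraph takes the quantities for the six-month costs from the HSSUI and names no other quantity source.

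Analysis: effectiveness evaluation identifies acute care episodes from both IC/ES and the HSSUI, without an order of precedence. It compares change in use and cost between arms with a non-parametric test. On missing data it says: "Multiple imputation will be used to address missing data".

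**The concern.** Three statements do not fit together. The HSSUI is a back-up in one paragraph and the only stated source of cost quantities in the next. Table 1 restricts the row to complete cases while the text promises imputation. Linked records, which do not depend on an interview taking place, are given no stated role in costing.

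The HSSUI is answered by participants at the assessments, and the test compares change between assessments. A missing interview therefore removes a participant from an HSSUI-based complete-case cost comparison. The population is aged 65 or over, recently in hospital, with several chronic conditions and depressive symptoms. It is plausible that people who miss interviews use acute care differently from those who complete them.

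The outcome is secondary but important to the trial's message. Lower use of expensive services is part of the hypothesis, and the Discussion presents the cost analysis as one of four main contributions.

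**Working it through.** **1. The plan's own figure.** Inputs, from Sample size: "which assumes a power of 80%, alpha of 0.05, mean MCS score difference of 6.5, standard deviation of 15.0 and 20% attrition". Allocation, from Randomization and blinding: "using a 1:1 ratio". Two-sided testing is assumed.

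- n per arm = 2 × (1.96 + 0.8416)² × 15² / 6.5² = 83.6, so 84; total 168.
- Allowing for attrition: 168 / 0.8 = 210. With the t distribution, 85 per arm: 170 / 0.8 = 212.5, so 213.
- The protocol states "The target sample size of 216 (72 from each of the three sites"; 3 × 72 = 216. The figure reproduces to within 3%. It concerns MCS; no power is stated for service use or costs. Only the 20% attrition is carried forward.

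**2. Who leaves the cost comparison.** The change from T1 to T2 needs interviews at both, and the change from T2 to T3 likewise. A missed T2 interview removes a participant from both comparisons; a missed T3 interview removes them from the second.

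- Lost at 20%: 216 × 0.20 = 43.2, about 43 (108 × 0.20 = 21.6 per arm).
- Retained: 216 × 0.80 = 172.8, about 173 (86.4 per arm).

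This is an upper figure for avoidable loss. It assumes the MCS attrition applies to the HSSUI interview and that everyone lost could be linked.

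**3. Precision.** Interval width scales as 1/√n: 1/√0.8 = 1.118, about 12% wider than if all 216 were analysed. For a risk difference with equal event risk p in both arms (assumed), the 95% half-width is 1.96 × √(2p(1 − p)/n):

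| Assumed p | n = 86.4 per arm | n = 108 per arm |
|---|---|---|
| 0.20 | 0.119 | 0.107 |
| 0.50 | 0.149 | 0.133 |

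**4. Possible bias, by assumption only.** The protocol gives no cost distribution or event risk. Suppose the risk of an acute event is 35% in control completers and 25% in CAST completers, so the complete-case risk difference is −0.10. Let non-completers in both arms have risk q, from 0.30 to 0.90. With d the proportion lost, the risk in each arm is (1 − d) × completer risk + d × q.

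| Loss, control / CAST | Difference in all randomised | Over q = 0.30 to 0.90 |
|---|---|---|
| 20% / 20% | 0.8 × (−0.10) | −0.08 throughout |
| 25% / 15% | −0.05 − 0.10q | −0.08 to −0.14 |
| 15% / 25% | −0.11 + 0.10q | −0.08 to −0.02 |

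The complete-case −0.10 can be too large or too small. With equal loss, the shift to −0.08 arises only because the example gives non-completers the same risk in both arms. The table describes the risk difference only if the complete-case rule were applied to it on interview completers, which the document leaves open.

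**5. What linkage can and cannot replace.** On the protocol's lists, IC/ES covers emergency visits, admissions, family physicians, specialists, home care and long-term care transfers. The HSSUI also asks about prescribed medications, lab services and seven types of other professionals, none of which is on the IC/ES list. Linkage is described for participants, and caregivers are not named. Linkage can therefore supply a large part of the cost quantities, but not all.

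**The case against.** Costing from the HSSUI has good reasons. The perspective is societal, the inventory reaches services that the IC/ES list does not, the unit prices were obtained for it, and access to IC/ES data was uncertain. Table 1 can also be read as qualifying the one-line imputation sentence, since other rows are complete case only too. These arguments stand as reasons to keep the HSSUI. They do not explain why a stated back-up is the only cost source for services that linkage would record, and the imputation sentence carries no exception.

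A reader might infer more than the document supports:

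- **That acute care events are confined to interview completers.** Episodes come from IC/ES as well as the HSSUI, so a linked participant who misses an interview need not be a missing case, and a hazard ratio can use censored follow-up. In the table cell, complete case follows the Mann-Whitney test; whether it governs the hazard ratio and risk difference is unclear.
- **That people who die or enter institutional care are certainly dropped.** No sentence says so. Discharge to long-term care is an exclusion only at entry, telephone assessment is allowed, and proxy respondents are foreseen. The handling of deaths is not stated, which an article may leave to a fuller plan.
- **That data already in hand are being thrown away.** Linkage is planned, and the text allows for not obtaining it.
- **That an intention-to-treat claim for this outcome is broken.** The analysis section ties intention-to-treat to the ANCOVA of continuous outcomes, and the Discussion names it only as a general strength.

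**Conclusion.** The point holds in limited form and rests on stated choices, not on detail an article would omit. Service use and costs are complete case only in both periods, cost quantities come from an interview-based instrument that the same section calls a back-up, and the row conflicts with an unqualified imputation sentence. For costs, missing an interview means leaving the comparison even where linked records cover much of the use.

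The size is up to about 43 of 216 participants, and intervals about 12% wider than with everyone analysed, if the 20% attrition applies to these interviews and all participants can be linked. Bias arises if loss is related to use and differs by arm. Its size and direction are unknown, and the ranges above are assumptions, not estimates. The outcome is secondary, but the change is worth making because the cost result carries much of the policy argument.

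**What to change.** 1. **Source.** For older adult participants, name IC/ES as the primary source for each service it covers, in use and in costs.
2. **Analysis set.** For those services, analyse all randomised linked participants regardless of interview completion, including the 30-, 90- and 180-day hazard ratios and risk differences.
3. **Death.** State how it is handled: for example, censoring for the hazard ratio with a competing-event sensitivity analysis, and an explicit rule for the risk difference and for costs.
4. **HSSUI.** Keep it for services IC/ES does not list (medications, labs, other professionals), for caregivers, and as back-up if linkage fails, with multiple imputation alongside complete case.
5. **Table 1.** Amend the row so that it agrees with the imputation sentence in the analysis section, and make clear which listed methods any complete-case label governs.

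The cost is moderate because linkage is already planned. The analysis becomes dependent on the timing and availability of the linked extract. Added work includes matching unit prices to IC/ES counts and stating how the rank test is combined across imputed datasets.

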**Methods:**

Participants will be considered eligible if they are > 65 years, planned for discharged from hospital to the community in three Ontario locations, self-report at least two chronic conditions, and screen positive for depressive symptoms. A total of 216 eligible and consenting participants will be randomly assigned to the control (usual care) or intervention (CAST) arm. The intervention consists of tailored care delivery comprising in-home visits, telephone follow-up and system navigation support. The primary measure of effectiveness is mental health functioning of the older adult participant. Secondary outcomes include changes in physical functioning, depressive symptoms, anxiety, perceived social support, patient experience, and health and social service use and cost, from baseline to 6- and 12-months. Caregivers will be assessed for caregiver strain, depressive symptoms, anxiety, health-related quality of life, and health and social service use and costs. Descriptive and qualitative data from older adult and caregiver participants, and the nurse interventionists will be used to examine implementation of the intervention, how the intervention is adapted within each study region, and its potential for sustainability and scalability to other jurisdictions.

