#### Analysis: effectiveness evaluation

Descriptive statistics will be used to summarize outcome values at baseline, 6 months and 12 months. Means and standard deviations will be used for continuous outcomes, and frequency and percentages will be used for categorical outcomes. Intention-to-treat analyses using analysis of covariance (ANCOVA) will be used to assess group differences in continuous outcomes from baseline to T2 in order to determine if the intervention was effective over the intervention period. The outcomes include: PRQ-2000, CESD-10, GAD-7, VR-12 PCS, VR-12 MCS, the PPC, CCCQ, and the IC-PREMs. The ANCOVA model will use the 6-month outcome value as the dependent variable, the group indicator as the independent variable and the baseline outcome value as the covariate. Model results will be expressed as mean group differences with accompanying 95% confidence limits. Quantile regression will also be used to examine the treatment effect over a broader range of values (beyond the mean) for the outcome variables. Assessment of group differences in continuous outcomes from T_2_ to T_3_ will be assessed using ANCOVA and will be aimed at assessing the sustainability of the intervention effects (see Table 1).

Z tests of proportions and McNemar tests will be used to assess changes within each group in the number of participants with acute care episodes and the number of acute care episodes from baseline to T_2_, and from T_2_ to T_3_ Acute care episodes include emergency department visits and hospital admissions. Risk difference (intervention risk – control risk) and accompanying 95% confidence limits will be calculated for 6 months for emergency department visits and hospital readmissions for 6 months. As was noted earlier, acute care episodes will be identified using administrative data from IC/ES, and self-reported data from the HSSUI. Due to the highly skewed nature of cost data, a non-parametric test will be used to compare the change in health and social service use and costs from baseline to T_2_ and from T_2_ to T_3_ for the two groups. Outliers are particularly common for certain healthcare costs such as hospital admissions, thus we will conduct a sensitivity analysis to assess the impact of outliers on the cost comparison.

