Fourth, objective, reliable and valid measures will be used to assess a variety of patient-relevant outcomes, addressing a gap in the current literature that focuses predominantly on hospital readmissions as an outcome. Fifth, the study will evaluate the sustainability of the intervention effects by measuring the effectiveness of the intervention 6-months following completion of the intervention. Sixth, intervention fidelity will be enhanced by multiple approaches. Notably, the CTCs will be provided training, a standardized training manual, and regular meetings held with the research team throughout the intervention period to enhance the fidelity of intervention implementation. Lastly, the intervention will be evaluated in multiple sites and in diverse communities, which will enhance the generalizability of the results to other settings, as it reflects the diversity of the target population.

Conversely, there are some limitations to the study that warrant acknowledgement. First, sampling bias may influence the results, as those who volunteer to participate may be more likely to be receptive to the intervention. We will assess the extent of non-response bias by comparing the characteristics of study participants to those who decline participation in the study on their characteristics at baseline. Second, the use of a proxy respondent as a source of data for the study participants with limitations in cognition, physical health or language, may result in either an overestimation or an underestimation of the results.

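### Between-arm effect estimates for ED visits and admissions end at 180 days, and the T2-to-T3 change test that follows cannot stand in for the 12-month outcome

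*Protocol article*

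**What the plan says.** The abstract of the protocol article includes among the secondary outcomes "health and social service use and cost, from baseline to 6- and 12-months". The Discussion counts as a strength "measuring the effectiveness of the intervention 6-months following completion of the intervention".

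For ED visits and hospital admissions, the event-based between-arm estimates appear in the utilization row of Table 1, under T1-T2: "Hazard Ratio (95% CI) & Risk Difference (95% CI) for 30, 90 &180-day ED visits and hospital admissions". The T2-T3 entry in the same row drops both and reads "T2-T3 (Sustainability): Mann-Whitney U test, complete case analysis".

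The section Analysis: effectiveness evaluation matches this. Risk differences "will be calculated for 6 months for emergency department visits and hospital readmissions for 6 months". For acute care episodes, including those from T2 to T3, it says "Z tests of proportions and McNemar tests will be used to assess changes within each group in the number of participants with acute care episodes", which is not a comparison of the arms. For service use and costs, a non-parametric test will "compare the change in health and social service use and costs from baseline to T_2_ and from T_2_ to T_3_ for the two groups".

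The section on cost of health and social services plans linkage to IC/ES records for ED visits and admissions. It keeps the self-reported HSSUI as a back-up in case the team is "unable to obtain IC/ES data at all three timepoints".

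**The concern.** The outcome is stated to 12 months, but the estimates that would describe it (a difference in risk or a hazard ratio, with a CI) end when the intervention ends. What follows is a test on a change whose starting point, use up to T2, is itself affected by the treatment. Such a change does not measure whether the arms differ in months 6-12, nor whether they differ over the year. It measures whether the gap between them moved after T2.

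Lower use of hospital care is part of the trial's hypothesis. As the plan stands, a non-significant T2-T3 result could mean a benefit that held for the whole year or no effect at any time, and no estimate with a CI is named for the second half-year or the full year. If the change test is read as the sustainability result, a lasting benefit would be reported as absent and a fading one as a deterioration.

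**Working it through.** **What is named for each period (between-arm, acute care or use)**

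| Period | Effect estimate with CI | Test |
|---|---|---|
| Months 0-6 | Hazard ratio and risk difference at 30, 90 and 180 days | Mann-Whitney on change from baseline |
| Months 6-12 | None | Mann-Whitney on change from T2 to T3 |
| Months 0-12 | None | None |

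The z and McNemar tests are within-group and fill none of these cells.

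**Inputs.** From the article: 216 participants allocated 1:1, so 216/2 = 108 per arm. It gives no rates for ED visits or admissions and no sample-size figure for them, so there is no planned figure to reproduce. Assumed: control means of 0.6 admissions in months 0-6 and 0.5 in months 6-12; counts Poisson with gamma frailty of variance 1; no attrition; T2 and T3 values each cover the preceding six months.

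**Expected values.** Let control means be m1 and m2 and the rate ratios under CAST be r1 and r2 (months 0-6 and 6-12). The between-arm difference in mean T2-to-T3 change is

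D(change) = m2(r2 - 1) - m1(r1 - 1),

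whereas D(6-12) = m2(r2 - 1) and D(0-12) = m1(r1 - 1) + m2(r2 - 1).

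- Sustained 35% cut (r1 = r2 = 0.65): D(change) = -0.175 + 0.210 = +0.035; D(6-12) = -0.175; D(0-12) = -0.210 - 0.175 = -0.385.
- Effect that ends at month 6 (r1 = 0.65, r2 = 1): D(change) = 0 + 0.210 = +0.210; D(6-12) = 0; D(0-12) = -0.210.

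With m1 = m2, a constant effect gives D(change) = 0 exactly. The cancellation comes from the subtraction; the assumed rates decide only how complete it is.

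**Simulation.** 4,000 trials per scenario, two-sided Mann-Whitney at 0.05; percent significant for benefit / for harm:

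| Comparison | Sustained 35% cut | Effect ends at month 6 |
|---|---|---|
| T2-to-T3 change (planned) | 1.4 / 3.9 | 0.1 / 30.7 |
| Months 6-12 counts | 34.4 / 0.0 | 2.2 / 2.5 |
| Months 0-12 totals | 47.9 / 0.0 | 14.7 / 0.2 |
| Months 0-6 counts | 36.5 / 0.0 | 35.6 / 0.1 |

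Repeated runs put the planned test at about 5-6% in total under the sustained cut, which is chance level. With both control means at 0.5, it is significant in 5.6% (2.6 / 3.0), against 46.1% for 12-month totals and 33.9% for months 6-12 counts.

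**Precision of a 365-day risk difference.** Half-width = 1.96 x sqrt(2p(1 - p)/108). At p = 0.20: 1.96 x sqrt(0.32/108) = 0.107. At p = 0.50: 1.96 x sqrt(0.50/108) = 0.133. That is about 11-13 percentage points.

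**The case against.** A reader might infer that the randomised comparison stops at day 180 and that the trial can say nothing about acute care afterwards. The article does not support that. A two-group test of use is planned for T2-T3, as is an intervention-versus-control cost comparison for months 6-12, and both IC/ES and HSSUI cover ED and hospital use.

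Nor does the 31% in the fade scenario mean that the plan would find CAST harmful. The change test is there detecting that a benefit ended. Read together with the 180-day risk difference, it carries some information separating a fading effect from a lasting one, though without an effect size or CI. The low figure under a sustained effect is likewise the expected answer to a different question: whether the gap moved after T2. Both objections stand, and they show that the change test is a poor sustainability result when read alone.

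Table 1 does not itself say that the T2-T3 test is on change. If it were run on months 6-12 use, the cancellation would disappear. The analysis text does say change, however, and that is the only definition given.

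The 180-day horizon may also be deliberate: it matches the six-month intervention, T1-T2 is labelled treatment effect, and the hypothesis on hospital use has no time limit. This explains why 180 days is included. It does not supply an estimate for the 12-month outcome in the abstract. An analysis plan that is not shown could add horizons, but here table and text both fix the horizon and name the T2-T3 method, so this is more than detail left open.

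Two further inferences go too far. Scale-up conclusions would not rest on 6-month hospital data; they draw mainly on qualitative sources (Table 2). And 12-month IC/ES records are intended but not assured, since the article provides for not obtaining them.

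**Conclusion.** The point holds in this form: hazard ratios and risk differences with CIs for ED visits and admissions are specified only to 180 days; no between-arm effect estimate is named for months 6-12 or 0-12; and the one later comparison of use is defined on a change from which a constant benefit largely cancels. It concerns a secondary outcome and leaves the primary analysis untouched, but it should be corrected because the article states a 12-month outcome and promises to assess lasting effects.

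On size: under the assumed rates and a sustained 35% cut, the planned test is significant in about 5-6% of trials, against about 48% for 12-month totals and 34% for months 6-12 counts. These percentages depend on assumed rates, frailty and full follow-up; the direction of the problem does not. The 12-month total is not sufficient alone, since it also picks up an effect confined to months 0-6 (about 15% here), so the months 6-12 comparison is needed beside it.

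**What to change.** In the utilization row of Table 1 and in Analysis: effectiveness evaluation:

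- add the between-arm risk difference with 95% CI at 365 days, separately for ED visits and for hospital admissions;
- add the between-arm comparison of the number of episodes in months 0-12 and in months 6-12;
- name IC/ES as the source, with HSSUI as the back-up already provided for;
- state that the acute-care sustainability conclusion is drawn from these estimates and not from the T2-to-T3 change test. If that test is kept, describe it as a test of whether the difference between arms moved after T2.

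This takes a few lines of wording and no extra participants or interviews. The drawback is a few more secondary estimates, each with a wide interval: about 11-13 percentage points either side for the risk differences at assumed risks of 20-50%. At the same risk and number analysed, the planned 180-day risk difference has the same width.
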